**4.1 Ethical Considerations 17**

**4.2 Confidentiality 17**

**5.0 References 18**

**1.0 Background and Significance**

Public Health Burden: Cancer-Related Fatigue

Cancer-related fatigue (CRF) is one of the most distressing symptoms that a person living with a cancer diagnosis experiences[[1]](#endnote-2). The National Cancer Institute’s PDQ ® on CRF states that it is “the most common side effect of cancer treatment with chemotherapy, radiation therapy, or selected biologic response modifiers”[[2]](#endnote-3) . Many studies report the prevalence rate of CRF to be between 14% to 99% for survivors undergoing treatment and 19% to 82% for survivors post-treatment[[3]](#endnote-4), [[4]](#endnote-5), [[5]](#endnote-6), [[6]](#endnote-7), [[7]](#endnote-8), [[8]](#endnote-9). It is pervasive and affects a survivor’s quality of life, social relationships and daily activities. It also places significant hardships on the survivor by limiting how much he or she can work or gain access to the social networks, resources and care that are critical for living with a cancer diagnosis[[9]](#endnote-10). Factors that may be associated with CRF include cancer treatment, anemia, inflammation, medications, sleep disorders, nutrition and psychological distress. Studies have suggested that pharmacologic interventions, exercise, cognitive behavior therapy and education may be treatment strategies. However, none of these has proven to be significantly effective for relieving CRF symptoms.

Open-Label Placebo (OLP) Intervention

Although randomized placebo-controlled drug trials sometime show that placebos produce patient-reported outcomes that are indistinguishable from those observed with active compounds, it is considered unethical to use placebos in clinical practices because eliciting positive responses with placebos is thought to require deception (i.e., treating with biologically inactive compounds without consent) or concealment (e.g. in randomized trials).

However, three recent non-deceptive (open-label) placebo studies –where patients were told they were receiving placebo pills – demonstrated improvement in symptoms for patients with Irritable Bowel Syndrome (IBS) (N=80, Cohen’s d=.79), in depression scores for adults with Major Depressive Disorder (MDD) (N= 20, Cohen’s d=.54) and in pain severity for migraine sufferers[[10]](#endnote-11),[[11]](#endnote-12),[[12]](#endnote-13). While these studies indicate that open-label placebos (OLPs) can influence patient-reported outcomes, it is unknown whether the same holds true for symptoms of CRF for which there are no significantly efficacious treatments. In addition, it is suggested that a certain genetic variation of COMT Val158Met (met/met) correlates with dopamine metabolism and is a potential biomarker suitable for identifying placebo responders[[13]](#endnote-14). (Dopamine metabolism disorder is one of the biochemical mechanisms hypothesized to be a causal factor of cancer-related fatigue[[14]](#endnote-15)).

Significance of this Study: There are serious ethical challenges to using placebos in clinical practice because use involves deception or concealment. A non-deceptive or “open-label” placebo is a sound, safe strategy that harnesses placebo effects for clinical practice in a way that is ethical, transparent and with informed consent. This study is significant because:

(1) It offers a strategy to harness placebo effects in conditions that are prevalent but where there are no effective treatments. If placebo effects can be elicited without deception or concealment, a significant challenge will be removed for the ethical harness of placebo effects in clinical practice.

(2) It is an innovative application of a clinically important but newly developed non-deceptive placebo methodology.

(3) It is a potential treatment for CRF that currently has no efficacious treatment.

(4) It has access to UAB resources, support and expertise.

(5) It addresses an important and ongoing clinical problem that compromises optimal and safe care.

(6) It will provide information on feasibility, effect sizes and factors that contribute to the variability in placebo responses for cancer survivors with moderate to severe symptoms of CRF.

(7) If will provide information that can lead to a larger trial with a substantially longer follow up with a broader array of outcome measures (e.g., cost-effectiveness, potential biomarkers).

(8) It may lead to additional clinical intervention studies for cancer survivors with the potential of enhancing the effectiveness of existing treatments and/or reduce the burden of side effects (e.g., nausea, depression, and neuropathy).

**2.0 OBJECTIVES**

The purpose of this randomized-controlled, crossover pilot trial is to evaluate the feasibility, acceptability and effects of a non-deceptive (open-label) administration of placebo pills for treating CRF. If significant effects are found, we will later determine if the presence of a COMT Val18Met genotype variant predicts placebo responses.

**Primary Objective**

**Specific Aim 1**: Assess the feasibility of an Open-Label Placebo (OLP) for treating CRF in cancer survivors (CSs).

Hypothesis 1: An OLP will be perceived by the majority of CSs screened as credible and acceptable and we will meet our enrollment, retention and adherence targets.

**Secondary Objectives:**

**Specific Aim 2:** Evaluate whether an OLP reduces CRF severity and improves quality of life (QoL) in CSs compared to Observational Controls (OCs).

Hypotheses 2: Over the course of 49 days, CSs receiving the OLP will report significant declines in CRF severity and significant improvement in QoL scores compared to OCs.

**Supplementary Aim**: We will collect and store saliva samples so, should significant OLP effects be obtained, we can evaluate whether a potential biomarker (COMT Val158Met variant) associates with placebo responsiveness.

Hypothesis: The presence of the COMT Val158Met variations (met/met and val/val alleles) will correlate with the placebo responsiveness.

**3.0 INVESTIGATIONAL PLAN AND PROCEDURES**

**3.1 Study Design and Population**

We propose to conduct a pilot randomized-controlled, crossover trial to evaluate the feasibility, acceptability and effect of the open-label administration of placebo pills on CRF and associated psychosocial factors (e.g., emotional health, social health, quality of life, etc.) for cancer survivors (CSs) who have completed all cancer treatments yet continue to experience CRF. Additionally, in an exploratory manner, we propose to collect DNA saliva specimens that we intend to analyze in the future to identify potential biomarkers for predicting placebo responses.

To do this, we will use a 7-week, single site, two-parallel arm, randomized controlled crossover pilot study to determine the feasibility, acceptability and effects of an OLP on CSs who completed cancer treatments at least 6 months prior to enrollment in the study and report a fatigue score of 4 or greater on a 0-10 scale.

We will enroll 80 eligible CS participants who will be randomized into two groups of 40 (Group1 and Group2). In this crossover study, participants in Group1, will receive an OLP (placebo pill) for 21-days and Group2 (Observational Controls) will not. After a 1-week washout period, Group2 will receive the OLP for 21-days and Group1 (Observational Controls) will not (see Figure 1a: Study Design Schema).

**3.2 Participants and Recruitment**

**Participants**: We intend to screen and recruit a sufficient number of individuals in order to enroll 80 cancer survivors, over the age of 19 who received oncology treatments at UAB and who meet our inclusion/exclusion criteria.

**Recruitment:** The primary method for identifying potential participants for this study will be through medical records examination. We will attempt to get a listing of people who were treated for cancer by cancer stage between 2009 – 2016 from the UAB Tumor Registry, the Center for Clinical and Translational Science and IMPACT. We will then compare this record to concurring physician’s patient database and to medical records information contained in IMPACT to identify recruits who meet the inclusion and exclusion criteria.

In order to meet this goal, we will also solicit recruits who received treatment at UAB through the use of flyers, posters and advertisement in UAB newspapers, presentations to local support groups and organizations.

Once we identify a list of prospective participants, we will review the listing with the treating physician. Once the treating physician concurs, we will send the prospective participant a letter signed by both the physician and the PI to offer the opportunity of participating in a study that will test a new, natural, non-pharmaceutical treatment for relieving CRF symptom severity. The letter will contain an opt-out option that instructs recipients to call us if they are not interested and we will remove their name from our list. The letter will also explain that if we do not receive an opt-out call from them within a week, we will call them to explain the study further and invite them to participate. To facilitate recruitment, we plan to inform potential candidates that:

- Each participant will receive the OLP at some point during the 7-week study.
- Free parking will be available to help alleviate the associated costs of participation.
- Each participant completing up 4 study visits will receive up to $75.00 in the form of cash in appreciation for their time and effort.

**Screening**: During a telephone screening, prospective participants will be asked to rate their current fatigue severity (0=no fatigue; 10=extremely severe fatigue). Those who report moderate fatigue (4) and who meet the other inclusion criteria (see Section 3.4) will be told that they qualify for the study after information is verified in IMPACT. The participants will be informed that:

- They will receive “placebo pills” at some point during the study.
- In several studies, placebos have been found to be just as effective, if not more so, than many drugs being used to relieve pain, to treat depression, anxiety, sleeplessness and fatigue when used in placebo-controlled clinical trials.
- Current recommended CRF treatments have not demonstrated adequate effect for relieving CRF symptoms.
- Placebos have been tested and found to be effective for relieving fatigue and pain in patients with symptoms related to IBS and migraines.
- They will be reimbursed for parking expenses.
- They will receive up to $75.00 in the form of cash for participating in the study.

**Enrollment:** After we identify eligible participants and receive a positive indication of willingness to participate, we will ask them for demographic information during the screening call. As each participant is verified and enrolled into the study, he or she will be scheduled for a total of 4 clinical site visits. Once the participant is enrolled, we will mail all relevant measurement instruments, instructions and consent forms prior to the first scheduled clinical site visit or Day 1 of the study.

**3.3 Informed Consent**

Upon enrollment and before Day 1 of the study, we will mail the Informed Consent form to the enrolled participant to allow adequate time for review and question formulation. On Day 1 of the study at the beginning of the study visit, the research specialist will review the Informed Consent form with the participant and address all questions and concerns. If the participant still chooses to participate in the study, we will acquire his or her witnessed signature. We plan to assure that the Inform Consent explains the participants’ rights, in clear, simple language, that includes:

- Information on the type of study this is and why we are doing it.
- Information on the procedures we will use, as well as a description of the placebo pill, instructions on how to take the prescribed placebos and how to use the saliva collection kit.
- Information on any known discomforts or risks, any associated costs (i.e., transportation) and any associated benefits.
- Any standards of care that might provide relief even if the prospective participant chooses not to participate in the study, as well as how the risks and benefits of such options compare to placebos.
- Any clinically effective treatment for CRF that becomes available during this study.
- The opportunity to ask any questions about the study or the procedures involved.
- The opportunity to be told of new findings that could change willingness to consent.
- The participant’s right to withdraw consent to participate at any time, without penalty or retribution.
- Protections for and rights of participants provided by GINA regarding the collection and analysis of DNA specimens.
- What kind of specimens will be collected and the means of collection.
- What type of research will be done with the specimens.
- Whether the biological specimens will be shared with other investigators,
- Whether biological specimens will be coded or anonymized (no way of tracing back to participant/uncoded or code destroyed).
- Whether the participant may be contacted for additional consent.
- How long, if known, the biological specimens will be stored. (Short-term: current protocol only or other current research; Long-term: future studies on disease or condition, repository, etc.).
- Foreseeable risks or benefits to participants in the collection, storage and subsequent research use of specimens.
- What will be done with the biological specimens if the participant refuses permission (“anonymized”—stripped of identifiers--or destroyed?).
- What will be done with the research results. (Research results should not be placed in the individual participant’s medical record.)
- The right to receive a copy of any consent form used in relation to the study.
- The time and opportunity to decide freely whether to consent or not consent to participate in the study.

**3.4 Inclusion, Exclusion, and Withdrawal Criteria**

**Inclusion criteria**:

- CSs who are at least 19 years of age with Stage II-IV cancer who have completed primary treatment  6months and within 10 years and have no evidence of disease;
- Report ≥4 (moderate fatigue) on a 0-10 fatigue severity rating scale;
- Agree not to change any of their medications or treatments during the study. (Should medication change be medically necessary, we will note this and incorporate it into the data analysis. However, given the short duration of the study, we do not anticipate medication changes);
- Willingness to make 4 clinical site visits over the course of the 49-day study.

**Exclusion criteria**:

- Stage I disease;
- Anemia of Hg<8gm/dl;
- Uncontrolled diabetes, COPD, hypertension, ischemic heart disease, liver/kidney disease, autoimmune disease or psychiatric or cognitive disorders.

**Withdrawal criteria:**

This is an investigator-initiated, uncomplicated, randomized crossover trial, and the risks/hazards are considered minimal. If a study participant desires to withdraw from the study, for whatever reason, they will be withdrawn.

**3.5 Randomization and Interventions (if applicable)**

A randomized assignment will be placed in an envelope that will be opened by the intervention administrator during the participants’ first clinical site visit (Day 1 of the study). Until that time, the intervention administrator will be blinded to the randomized assignment until it is revealed to the participant. However, because of the “open disclosure” of placebo use, study assignments cannot be blinded to the intervention administrator or to the participant once the envelope is opened. To control bias, the intervention administrator will have limited contact with the participants after Day 1 with the exception of a brief “re-orientation” on Day 28 at the beginning of Period 2 .

On Day 28, participants originally assigned to Group2 will receive the OLP and be prescribed two placebo pills twice a day to take over the course of 3 weeks (21 days). The participants who were randomly assigned to Group1 will serve as the NO OLP observational controls over the course of 3 weeks (21 days).

Figure 2: Crossover Study Arms

**Intervention: Placebo Orientation Meeting (Day 1 of Study / 1st Clinical Site Visit)**

At the beginning of the first clinical site visit (Day 1 of Study) the research specialist will acquire informed consent from the participant. Once the participant has provided his or her consent, the research specialist will review the four questionnaires with the participant, address any questions or concerns and ask the participant to complete each instrument. After reviewing the questionnaires for missing data, the research specialist will label each completed questionnaire with the appropriate study numeric identifiers and store the questionnaires in a secured unit for future analysis. The research specialist will then instruct the participant on how to use the ORAGENE® Discover (OMR-500) saliva collection test kit and a saliva sample will be collected, labeled with the appropriate study identifiers and stored in a secured unit for future analysis. The research specialist will schedule all 3 subsequent clinical site visits (Days 21, 29 and 49) and introduce the participant to the intervention administrator.

The intervention administrator will deliver a persuasive rationale for the OLP to the participant as part of the OLP Orientation on Day 1. The persuasive rationale (OLP orientation) is a critical component of this study and will be presented to participants in a way that fosters positive expectations, without deception, when a placebo is delivered. The script for the persuasive rationale includes dialogue that:

- Supports positive expectations and trust with an accurate description of what is known about placebo effects;
- Allows for contradictory thoughts including doubt and disbelief; and,
- Encourages adherence to the medical ritual of pill taking.

Four main discussion points will be included in *a priori* script that takes approximately 20 minutes to deliver (see Table1). The introduction will begin with a question:

- “Have you ever heard about placebo effect prior to our discussion on the phone?” followed by a natural give-and-take discussion.
- The practitioner will explain (or support the patient’s understanding) that “placebo pills are made of an inert substance, like sugar or starch, that has been shown in clinical studies to produce significant improvement in a variety of symptoms including fatigue and pain, through mind-body, self-healing processes that our bodies can naturally do.”
- This exchange will lead the intervention administrator to explain the four main discussion points of the persuasive rational.

| **Table 1: Four Discussion Points of the Placebo Orientation Meeting** |
| --- |
| **Placebo Effect/Expectancy Building**: Explain how Medicine is learning to respect the power of placebo effect and how our team has demonstrated that placebo treatment can lead to substantial relief whether placebo is concealed or unconcealed. **This segment is designed to build patient expectancies.** |
| **Conditioning**: Explain how the body can respond automatically to placebo pills naturally by releasing chemicals like dopamine to relieve pain. Placebos have been shown to produce physiological responses that are independent of conscious belief. We will mention examples of conditioned placebo responses such as immunology and endocrinology as well as pain conditions like those associated with migraine headaches, arthritis and irritable bowel syndrome. **This segment seeks to reassure patients that response to placebo can produce legitimate changes in physiology.** |
| **Realistic Attitude Towards Belief/Disbelief:** Explain that positive expectations can be helpful but not necessary. Participants need to be comfortable with contradiction and ambiguity because their beliefs may way and wane during the trial. **This segment seeks to reassure patients that belief and disbelief are both compatible with placebo response and comfort with either is important.** |
| **Emphasize Automatic Importance of Adherence**: Explain that studies show that people who take placebo pills faithfully do much better than those who do not. **Our experience and pilot work suggests that enlisting patient commitment to performing the ritual of the treatment may be more important than the cognitive components of the script. Adherence also supports the conditioning dimension of the placebo.** |

The delivery of the persuasive rationale will be audio-recorded in all patients for use in establishing fidelity to treatment. Because of the importance of the interaction between the intervention administrator and the participant, all interactions will take place in the context of a warm, supportive and natural interaction. The importance of the no-treatment control group will also be discussed and questions will be answered. After the placebo orientation, the envelope with the randomized assignment will be opened and both the participant and the intervention administrator will learn which group the participant will join.

**Group1**: Participants assigned to Group1 will be given a pre-filled, twice-per-day weekly pill organizer. The intervention administrator will instruct Group1 to “take 2 pills in the morning with breakfast and two pills in the evening before bedtime.” The placebo pills will be blue and maroon gelatin capsules filled with non-absorbable Avicel® (Microcrystalline cellulose), a common inert excipient for pharmaceuticals. Prior to departing, the participant will ingest two of the placebo pills and be given a medication diary with instructions to record each time placebos are taken so that a pill count can be made.

**Group2**: Participants assigned to Group2 will be reassured that they will receive the OLP during Period 2 of the study. The intervention administrator will also reiterate the importance of the role of observational controls.

Parking tickets will be stamped and participants will be provided contact information for study team member and IRB should they have questions or concerns. They will be given a reminder card with their next appointments (Day 21, Day 29 and Day 49). They will also be told to expect a follow up telephone call from a study team member midway through Period 1 on or about Day 11. The estimated time for the first clinical site visit (Day 1) is 60 minutes.

**Mid-Point Check-In Call:** participant is called to check on condition. Calls lasts < 5 minutes.

**End of Period 1 (Day 21 of Study / 2nd Clinical Site Visit**): Study participants will be instructed to return to the clinical site on Day 21 of the study. At that time, the research specialist will collect the medication diaries and address any questions or concerns. The research specialist will administer the 4 questionnaires that will be labeled with the appropriate study identifiers and stored in a secured unit for future analysis. Participants will be reminded of their next clinical site visits (Day 29 and Day 49) and parking tickets will be stamped. Once again, participants will be reminded of the value of their participation. The estimated time for the 2nd clinical site visit is 25 minutes.

**Beginning of Period 2 (Day 29 of the Study / 3rd Clinical Site Visit):** On Day 29, participants will return to the study site to begin Period 2 of the trial. The research specialist will review the 4 questionnaires with the participant, address any questions or concerns and ask the participant to complete each instrument. The research specialist will label each completed questionnaire with the appropriate study numeric identifiers and store the questionnaires in a secured unit for future analysis. The intervention administrator will meet with participants to explain procedures for Period 2.

**Group1** : participants will be informed that they are now the OC and the value of that role will be reiterated. They will be reminded of their next clinical site visit and told to expect a follow up call at some point (on or about Day 39). Parking tickets will be stamped and the participant will be provided a reminder of the next (and final) clinical site visit (Day 49 of the study).

**Group2** : participants will be informed that they will now receive the OLP. The intervention administrator will re-present a brief version of the rationale for the OLP and remind participants of the 4 main points from the original orientation meeting. Participants will be encouraged to ask questions and discuss concerns. Participants assigned to Group2 will be given a pre-filled, twice-per-day weekly pill organizer. The intervention administrator will instruct Group2 to “take 2 pills in the morning with breakfast and two pills in the evening before bedtime.” The placebo pills will be blue and maroon gelatin capsules filled with non-absorbable Avicel (Microcrystalline cellulose), a common inert excipient for pharmaceuticals. Prior to departing, the participant will ingest two of the placebo pills and be given a diary with instructions to record each time placebos are taken so that a pill count can be made. They told to expect a follow up call at some point (on or about Day 39). Parking tickets will be stamped and the participant will be provided a reminder of the next (final) clinical site visit (Day 49).The estimated time for the Day 29 clinical site visit is 35 minutes.

**Mid-Point Check-In Call:** participant is called to check on condition. Calls lasts < 5 minutes.

**End of Period 2/End of Study (Day 49):** Study participants will return to the clinical site on Day 49 of the study. At that time, the research specialist will collect the medication diaries and address any questions or concerns. The research specialist will administer the remaining questionnaires and assure that all questionnaires are stored in a secured unit for future analysis. The intervention administrator will meet briefly with participants to thank them for their participation and to distribute cash incentives. Parking tickets will be stamped. The estimated time for this visit is 25 minutes.

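### At Day 21 and Day 49 the protocol lists diary hand-in ahead of the fatigue and QoL questionnaires, and only participants on OLP have a diary to hand in

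*Protocol*

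**What the plan says.** Section 3.5 describes each clinic visit as a list of tasks. For both end-of-period visits (Day 21 and Day 49) the first task after the participant's return is: "At that time, the research specialist will collect the medication diaries and address any questions or concerns". At Day 21 the next sentence begins: "The research specialist will administer the 4 questionnaires that will be labeled with the appropriate study identifiers". At Day 49 it is: "The research specialist will administer the remaining questionnaires and assure that all questionnaires are stored in a secured unit for future analysis".

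Diaries go only to the group on OLP. In Period 1, Group1 participants will "be given a medication diary with instructions to record each time placebos are taken so that a pill count can be made". In Period 2, Group2 participants will "be given a diary with instructions to record each time placebos are taken so that a pill count can be made". The text for the group serving as observational controls mentions no diary or comparable task in either period.

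Table 1 in the same section gives the script for the Day 1 orientation, which is delivered before the assignment is opened. On adherence it tells the intervention administrator: "Explain that studies show that people who take placebo pills faithfully do much better than those who do not".

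The bias control stated in section 3.5 is: "To control bias, the intervention administrator will have limited contact with the participants after Day 1", with an exception for the brief re-orientation at the start of Period 2. It does not address the order of tasks at the visits where outcomes are collected.

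**The concern.** Every Aim 2 outcome in section 3.6.2 is a self-report questionnaire, and the comparison is open-label placebo against no treatment. Such ratings are open to cues about what the participant is expected to report. Handing in a record of pill-taking immediately before the rating, after being told that adherence goes with improvement, is a cue of that kind, and only the OLP side receives it.

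At stake is how cleanly the Aim 2 contrast can be read. Section 1.0 says the pilot is to provide effect sizes and may lead to a larger trial. The COMT analysis goes ahead only if significant OLP effects are found. No later analysis can remove a cue that coincides exactly with treatment, so it has to be dealt with in the visit procedure.

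**Working it through.** The plan gives no figure for this point, so the check is a comparison of the text, with one line of algebra for the crossover.

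**1. Order within the visit.** At Day 21 and Day 49 the diary-and-concerns sentence comes directly before the questionnaire sentence, and the same role does both. No word such as *before* or *then* links the two. The Day 1 description does use sequence words. The order is therefore listed but not fixed, and nothing puts the questionnaires first.

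**2. Who has a diary to hand in.**

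| Visit | Group1 | Group2 |
|---|---|---|
| Day 21 (end of Period 1) | on OLP, diary | control, no diary |
| Day 49 (end of Period 2) | control, no diary | on OLP, diary |

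**3. What differs between the groups.** Addressing questions or concerns is described for all participants, so on the text it is common to both groups. The diary hand-in is the only listed step that differs.

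**4. Whether the crossover removes it.** Let τ be the OLP effect, h any effect of the hand-in on the rating, and π1 and π2 the period effects. Leave carryover aside. Expected end-of-period ratings, apart from a common mean, are:

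- Group1: π1 + τ + h at Day 21; π2 at Day 49. OLP minus control = τ + h + (π1 − π2).
- Group2: π1 at Day 21; π2 + τ + h at Day 49. OLP minus control = τ + h + (π2 − π1).
- Average of the two: τ + h.

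The period effects cancel and h does not. The Day 21 between-group contrast used for the sample size is also τ + h.

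**5. Whether h can be sized.** The only design effect in section 3.7 is 0.64, with 80 participants. That calculation reproduces: a two-sided t-test at 0.05 with 80% power needs 39.3 per group, so 40 per group and 80 in total, and power at 40 per group is 80.7%. It says nothing about h. No passage gives a value for h or fixes its sign.

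**The case against.** The case for leaving the text alone has several parts, and much of it stands.

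- **The order is only inferred.** This is correct, and it is why the point is that questionnaires-first is not secured, not that the protocol mandates the opposite. Task order can be left to a site manual. But section 3.5 already sets out the visit step by step, and staff following it would probably collect diaries first.
- **The cue adds little.** Participants know their assignment, are told to take pills twice a day and record each intake. Section 3.5 openly says that they cannot be blinded. The hand-in is one more reminder among many. This stands and keeps the point small.
- **The visit leaves little room for discussion.** Day 21 and Day 49 are each estimated at 25 minutes, and section 3.6.2 gives 25 minutes for the questionnaires alone. This argues against a long conversation beforehand, but does not touch the hand-in itself.
- **The direction is open.** A diary with missed doses might lower expectation after the adherence message. This also stands.

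A reader might infer three stronger claims that the protocol does not support:

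- **That Day 1 and Day 29 run in the reverse order.** At both visits the research specialist also addresses questions or concerns before the forms are completed. No diary is collected at either, so there is no order to reverse.
- **That an assessor's blinding is broken.** When the envelope is opened, "both the participant and the intervention administrator will learn which group the participant will join". The research specialist is not named there, but is nowhere described as blinded, and administers self-report forms rather than rating fatigue.
- **That reordering would keep the specialist unaware of assignment.** It would not. Receiving a diary at Day 21, even after the questionnaires, reveals the sequence and so the assignment in Period 2.

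**Conclusion.** The point holds as a minor one. As listed, the end-of-period visits place an adherence hand-in on the OLP side only, just ahead of the self-reported Aim 2 outcomes, and nothing in section 3.5 prevents it. It adds an avoidable element to an expectation bias that is otherwise built into the design.

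This rests on two readings: that staff would follow the tasks in the order written, and that controls have no diary because none is described for them. It would be tempting to express the effect as a share of the 0.64 design effect or to call it a bias in favour of OLP. The protocol supports neither, so no magnitude is given. The primary endpoint of feasibility and acceptability, including adherence from pill counts and diaries, is not called into question.

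**What to change.** State in section 3.5 that at Day 21 and Day 49 participants complete the four questionnaires on arrival, before diaries are collected and before any discussion of pills or treatment. Questions about how to fill in the forms are excepted. Diary collection, other questions or concerns, and the per-visit safety and concomitant-medication checks in section 4.0 follow within the same visit.

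The change costs protocol wording only: same staff, same visits, same duration. The adherence data are still collected in full. It removes the listed difference in conditions just before the rating. It does not remove the participants' knowledge of their assignment, and should not be presented as blinding the research specialist.
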